### Intention-to-treat and imputation

Participants will be considered part of the intention-to-treat population if they were randomized at the start of the trial. If a participant has missing data for the outcome, then the median value for the treatment group will be imputed. To provide evidence of the robustness of the study results obtained from the above analyses, the same analyses will be repeated on two other data sets; one where imputation is done using the 75th percentile instead of the median, and another using the 25th percentile. These three sets of results will then be compared.

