#### Statistical analysis

Table 1 shows the planned statistical tests to be used for each variable investigated. The significance level will be set to α = 0.05 (two-tailed).

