**Table 1 Tab1:** **Statistical tests**

Outcome measure		Type of variable	Statistical test ***P***<0.05
**Primary outcome**	Duration of alignment stage for the upper and lower arches	Continuous, assuming normal distribution	One-way ANOVA test
**Secondary outcomes**	Number of visits required	Continuous, assuming normal distribution	One-way ANOVA test
	Occlusal outcome PAR	Continuous, assuming normal distribution	One-way ANOVA test
	Patient perception	Categorical data	Chi-square test
	Severity of OIIRR	Categorical data	Chi-square test or Friedman test

A list of statistical tests that will be used for data analysis depending on the type of data in the current trial. Peer Assessment Rating index (PAR), orthodontically induced inflammatory root resorption (OIIRR), analysis of variance (ANOVA).

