## Discussion

Orthodontic treatment with fixed appliances usually takes around two years to complete. Therefore this randomized controlled trial presents potential difficulties with participant dropout due to patients moving to other treatment centers and clinicians failing to obtain treatment records at key stages during treatment. Although it is not possible to prevent the former, the latter source of bias will be minimized by regular trial updates and reminders throughout the duration of the trial.

The results from the current study will serve as evidence to guide clinicians in deciding whether the difference in bracket slot size has a significant impact on the effectiveness of orthodontic treatment.

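### The median and quartile imputation rule is not limited to continuous outcomes; for root-resorption severity it gives every missing patient in an arm the same grade, which can distort the severe rate in either direction

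*Protocol article*

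**What the plan says.** All randomized participants form the intention-to-treat population. For missing values, the section on intention-to-treat and imputation in the protocol article states: "If a participant has missing data for the outcome, then the median value for the treatment group will be imputed". As a robustness check, "the same analyses will be repeated on two other data sets", namely "one where imputation is done using the 75th percentile instead of the median, and another using the 25th percentile". The three sets of results are then compared.

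The analyses that precede this section are those of Table 1, introduced by the sentence "Table 1 shows the planned statistical tests to be used for each variable investigated". Two of its five rows are typed as categorical: patient perception (chi-square) and "Severity of OIIRR" ("Chi-square test or Friedman test"). No separate missing-data rule is given for these two rows.

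The Secondary outcomes section reads OIIRR from periapical radiographs at nine months. The Stopping rule section defines severe OIIRR as loss of more than one third of the root. The Discussion expects dropout and also "clinicians failing to obtain treatment records at key stages during treatment".

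**The concern.** A median or quartile is a natural fill-in for months or PAR points. For a graded outcome it selects a single grade, and every patient in the arm without a usable film receives it. Three consequences follow.

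- **The reported severe rate moves.** The numerator gains either none or all of the missing patients, while the denominator grows to everyone randomized.
- **The robustness check can be empty.** If all three percentiles fall in non-severe grades, none of the three data sets can add a severe case. Their agreement then says nothing about severe harm.
- **The test can be disturbed.** If the two arms are filled with different grades, a block of identical values sits in a different cell in each arm, and the chi-square test treats it as real data.

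OIIRR is the only biological side effect among the listed outcomes, so an error in its severe rate matters to readers weighing the two slot sizes. The problem also differs from the understated variance that single-value imputation causes for a continuous outcome, because here the estimate itself is shifted.

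**Working it through.** **Inputs from the document.** 108 per group; 92 per group needed; 15 to 20% dropout; difference 3 months, SD 7.2, two-sided 0.05; the three imputation percentiles; OIIRR severity typed as categorical.

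**Inputs assumed.** The document gives no expected severe rate, no share of missing nine-month films and no grade distribution. Ranges are used for all three.

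**The plan's own figures.** The exact t-test calculation gives 91.4, so 92 per group, with power 80.3% at 92. For 15% dropout, 92 / 0.85 = 108.2, which agrees with 108 per group to within rounding (216 against 218 in total). With 108 per group, 15% missing leaves 92 observed and 16 imputed; 20% leaves 86 and 22; 5% leaves 103 and 5.

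**Step 1: which grade is filled in.** Let p be the severe share among observed patients in an arm. Severe is the top grade, so the q-th percentile is severe only if 1 − p < q.
- p below 25%: the 25th percentile, median and 75th percentile are all non-severe.
- p from 25 to 50%: the 75th percentile is severe.
- p above 50%: the median is severe as well.

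**Step 2: severe rate after imputation.** If the filled grade is non-severe, the rate is p × observed / 108. If it is severe, the rate is (p × observed + missing) / 108.

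| Observed p | Missing | 25th set | Median set | 75th set |
|---|---|---|---|---|
| 10% | 5% | 9.5% | 9.5% | 9.5% |
| 10% | 15% | 8.5% | 8.5% | 8.5% |
| 10% | 20% | 8.0% | 8.0% | 8.0% |
| 30% | 15% | 25.6% | 25.6% | 40.4% |
| 51% | 15% | 43.4% | 58.3% | 58.3% |

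For example, 0.10 × 92 / 108 = 8.5%, and (0.30 × 92 + 16) / 108 = 40.4%.

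**Step 3: severe versus non-severe between arms, 15% missing in each.**
- Both arms below 25%: 5/92 v 14/92 gives p = 0.029 on observed films; 5/108 v 14/108 gives p = 0.031 in all three sets. The test hardly moves, while the rates fall.
- One arm on each side of 25%: 18/92 v 28/92 gives p = 0.089 on observed films. In the 75th-percentile set the second arm gains all 16 missing patients, so 18/108 v 44/108 gives p = 0.0001.

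**Step 4: chi-square across four grades, identical arms.** Simulated with 108 per arm and missingness unrelated to grade. The grade distributions are illustrative.
- 25/25/40/10% (cumulative boundaries exactly at 25% and 50%): median-set rejection about 0.50 at 15 to 20% missing, against about 0.05 on observed films.
- 20/35/35/10% (boundary at 55%): median set about 0.25 to 0.29 at 15 to 20% missing.
- 30/40/20/10% (boundaries at 30% and 70%): median set about 0.05, but the two percentile sets about 0.25 to 0.3.
- 35/30/25/10% (no boundary near the median): median set about 0.04 to 0.065.
- With 5% missing, sets with a boundary near their percentile reach about 0.09 to 0.13.

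With 10% severe, the severe count was the same in all three sets in essentially every run.

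**Patient perception.** A percentile exists for an ordered response. For an unordered item it is undefined. The article does not show the response format.

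**The case against.** **Scope.** The rule speaks of the outcome in the singular, so a version meant for the primary outcome alone is not excluded, and the article condenses a fuller document. This stands as a caveat. However, the robustness sets are tied to the preceding analyses as a whole ("To provide evidence of the robustness of the study results obtained from the above analyses, the same analyses will be repeated on two other data"), and those analyses are Table 1. If only the primary outcome was meant, the text needs to say so.

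**Direction.** A reader might infer that severe harm will be understated in all three data sets. The document does not support that without a condition: it needs fewer than 25% severe in the arm, no rate is given, and above 25% the 75th-percentile set errs the other way. Understated here also means relative to the observed rate, which presumes that missing patients resemble those seen.

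**Nominal data.** A reader might also infer that the categorical outcomes are nominal, so that the rule is meaningless for them. Table 1 says only categorical, and severity is by name an ordered scale.

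**Missingness.** The 15 to 20% is dropout assumed for a treatment lasting about two years. Loss of nine-month films may be smaller, and at 5% the shift is half a percentage point on 10%.

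**False positives.** The figure near 0.50 comes from a boundary placed exactly on the percentile. Away from boundaries the rate stays near 0.05, so the accurate claim is instability near a boundary.

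**Patient protection.** Adverse events are recorded throughout appliance wear, a committee meets every three months, and the stopping rule acts on what radiographs show and does not mention imputed values. Nothing indicates that safety monitoring is affected; the issue concerns the reported analysis.

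**Conclusion.** The point holds in conditional form. The rule is not confined to continuous outcomes and, on its natural reading, reaches the two categorical rows of Table 1. For OIIRR severity it assigns one grade to all missing patients in an arm.

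- Below 25% severe, the severe rate becomes p × (1 − missing) in all three data sets, a relative reduction of 5% with 5% missing and 15 to 20% with 15 to 20% missing. The sensitivity sets cannot reveal it.
- From 25 to 50% severe, the 75th-percentile set overstates; above 50%, the median set does too.
- The chi-square test is close to nominal unless a grade boundary lies near the percentile used. There, false positives rise to about 0.09 to 0.13 with 5% missing and about 0.25 to 0.50 with 15 to 20% missing.
- For any unordered patient-perception item, the rule cannot be carried out.

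The sizes rest on assumed severe rates, grade distributions and missing-film shares. That a single grade is filled per arm does not rest on them. OIIRR is a secondary outcome, so this should be corrected but does not threaten the primary comparison.

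**What to change.** State that the median and percentile rule applies to continuous outcomes only. For OIIRR severity and patient perception, analyse the observed categories and report the number missing in each arm. As the sensitivity analysis, use either multiple imputation with an ordinal model or best-case/worst-case bounds; for severe OIIRR, count missing patients as severe in one arm and non-severe in the other, then reverse. For an unordered perception item, use the bounds.

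The cost is a few sentences of analysis text and some extra table rows; no new data are needed. The harm estimate will be less precise and possibly less favourable.

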### Target sample size

The sample size calculation is based on the primary outcome of duration of orthodontic treatment. Using nQuery Advisor 7.0 sample size was calculated to detect a difference in mean treatment duration of three months (clinically important difference). Standard deviation was estimated using the studies of Amditis and Smith [5] and Eberting et al. [12]. A sample size of 92 in each group will have 80% power to detect a difference in means of three months assuming that the common standard deviation is 7.2 using a two group Student’s *t*-test with a 0.05 two-sided significance level. Assuming a 15 to 20% dropout rate, we will recruit a total of 216 patients.

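### The robustness reruns move missing outcomes the same way in both arms, so with similar dropout shares they say little about loss that biases the comparison

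*Protocol article*

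**What the plan says.** The Protocol article, section Intention-to-treat and imputation, defines the population by randomization: "Participants will be considered part of the intention-to-treat population if they were randomized at the start of the trial". It then fixes the rule for missing outcomes: "If a participant has missing data for the outcome, then the median value for the treatment group will be imputed".

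The sensitivity analysis follows, with its purpose: "To provide evidence of the robustness of the study results obtained from the above analyses, the same analyses will be repeated on two other data" (here the quote breaks off). The two reruns are described as "one where imputation is done using the 75th percentile instead of the median, and another using the 25th percentile. These three sets of results will" (the sentence ends with the comparison of all three). Each set names one percentile and none treats the arms differently. That each arm's own percentile is meant follows from the median rule, although this is not repeated for the two reruns.

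The section Target sample size gives the expected loss as one overall figure: "Assuming a 15 to 20% dropout rate, we will recruit a total of 216 patients". No rate by arm is given. The Discussion names two expected causes, moves to other centers and records that clinicians fail to obtain, and ties neither to an arm.

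**The concern.** A sensitivity analysis for missing data should vary the assumption that could change the conclusion. In a two-arm comparison, that is how the missing patients in one arm differ from the missing patients in the other. If unobserved patients in both arms run longer than observed ones by the same amount, and the shares lost are equal, the difference between arms is not biased. If they run longer in one arm only, it is biased.

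The planned reruns vary only the common assumption: everyone missing is slow, or everyone missing is fast. Every set is also anchored to the values observed in each arm, so any selection in who remains observed carries into all three. Agreement could then be read as reassurance about a bias that the reruns hardly probe. This is separate from the understated standard error of single imputation and would remain if the standard errors were right.

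**Working it through.** **Inputs.** From Target sample size: "A sample size of 92 in each group will have 80% power to detect a difference in means of three months", with "common standard deviation is 7.2 using a two group Student’s *t*-test with a 0.05 two-sided significance level", and 15 to 20% dropout. From the Abstract: 108 per arm. Assumed here, because the article does not give them: the split of dropout by arm, normality, a mean of 24 months (the Discussion says about two years), and the mechanisms of loss.

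**The plan's own figure.** The normal approximation gives n = 2 x (1.960 + 0.842)² x 7.2² / 3² = 90.4, so 91 per arm. The t-test solution is 91.4, so 92, with power 80.3%. The stated 92 reproduces, and SD 7.2 and the three-month target are used below.

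**How far each rerun moves the difference.** After filling, an arm mean is (1 - m) x observed mean + m x fill value. Going from the median to the 75th percentile changes one filled value by 0.6745 x 7.2 = 4.86 months, and the arm mean by 4.86 x m. Hence:

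- same direction in both arms: shift in the difference = 4.86 x (m1 - m2)
- opposite directions: shift in the difference = 4.86 x (m1 + m2)

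| Share missing, arm 1 v arm 2 | Same direction, months (absolute) | Opposite directions, months |
|---|---|---|
| 15% v 15% | 0 | 1.46 |
| 20% v 20% | 0 | 1.94 |
| 15% v 20% | 0.24 | 1.70 |
| 10% v 25% | 0.73 | 1.70 |
| 5% v 30% | 1.21 | 1.70 |

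**What bias depends on.** Let g be the mean of the missing minus the mean of the observed in an arm. With a median fill and a roughly symmetric distribution, the bias in the difference is about -(m1 x g1 - m2 x g2). With equal shares m it is -m x (g1 - g2). The planned reruns set g1 = g2 at +4.86 or -4.86, so g1 - g2 stays at zero. The opposite-direction reruns set g1 - g2 at plus or minus 9.71.

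**Simulation.** 4000 trials per row, 108 per arm, no true effect, own-arm fill, t-test. The chance of loss is proportional to exp(s x standardized duration): s = 1 is moderate, s = 2 strong, a negative s means that short cases are lost, and s = 0 is random loss.

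| Missing; s in arm 1, arm 2 | Mean difference: median, 75th, 25th | Opposite fills: 75th/25th, 25th/75th | Three verdicts agree |
|---|---|---|---|
| 17.5% each; 0, 0 | -0.01, 0.00, -0.01 | 1.67, -1.69 | 94% |
| 17.5% each; 2, 0 | -1.74, -1.87, -1.66 | -0.19, -3.34 | 88% |
| 17.5% each; 1, -1 | -2.38, -2.39, -2.39 | -0.83, -3.96 | 91% |
| 15% v 20%; 2, 0 | -1.51, -1.87, -1.19 | 0.07, -3.13 | 75% |
| 5% v 30%; 0, 0 | -0.01, -1.20, 1.19 | 1.63, -1.65 | 42% |

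In the second and third rows a false difference of 1.7 to 2.4 months barely changes across the planned sets. By the formula, the third row needs g1 - g2 = 2.38 / 0.175 = 13.6 months, which is a large gap. In the last row the planned sets do separate.

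**The case against.** The case for leaving the check alone has five parts.

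- **It is not blind to dropout in general.** A reader might infer that the shift always cancels and that the sets agree whatever the dropout. They do not. At 10% v 25% random loss the three verdicts agree in about 72% of trials, and at 5% v 30% in about 44% (42% in the run tabulated above). Even at 15% v 20%, agreement can drop to 75%. This stands and limits the point to similar shares with similar spread.
- **The documents do not predict arm-specific loss.** The causes in the Discussion are not tied to an arm. Under Withdrawal procedures, participants given alternative treatment stay in follow-up and analysis. Slow cases lost from one arm and fast cases from the other is an illustration only. Allocation is open and treatment is long, so the possibility cannot be dismissed, but no more than that can be said.
- **No decision rule is stated.** A reader might infer that the plan will declare a biased difference robust. The article only offers the reruns as evidence and says that the results will be compared, and a fuller analysis plan may add to this. What stands against the article is that the comparison it does fix is weak for its stated purpose.
- **Agreement is not the same as error.** With moderate loss of slow cases from one arm and random loss from the other, all three sets are correctly non-significant in 71% of trials at 15% missing and falsely significant in 22%. At 20% missing the figures are 54% and 34%. Significance rates also carry the understated standard error: with random loss and no effect, 9 to 12% of trials reject. The argument therefore rests on the shift in the difference, not on these rates.
- **Opposite-direction reruns are a harsh test.** With a true three-month effect and 20% random loss, only about 30% of significant results survive both, close to the roughly 32% for a false difference under opposite mechanisms (s = 1, -1). Survival does not separate truth from bias. This stands and shapes the fix.

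**Conclusion.** The point holds in limited form. The stated reruns vary a common assumption that nearly cancels in the comparison of arms when the arms lose similar shares. The cancellation is exact at equal shares and spreads, and leaves about 0.24 months at 15% v 20%. Changing the assumption by arm at the same percentiles would move the difference by about 1.5 to 1.9 months, half or more of the three-month target. Agreement of the three sets is therefore weak evidence against bias from arms losing similar shares for different reasons. It is informative when dropout rates differ strongly.

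This concerns the sensitivity analysis and does not show that the trial result will be biased. The shift sizes rest on the plan's SD, normality and own-arm percentiles. The false differences rest on assumed mechanisms for which the documents give no figures.

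**What to change.** In Intention-to-treat and imputation, keep the three planned sets and add reruns in which the assumption differs by arm: the 25th percentile in the 0.018-inch arm with the 75th in the 0.022-inch arm, and the reverse. Preferably, use instead a delta-adjusted (tipping-point) analysis that varies the assumed mean of the missing patients separately in each arm, with standard errors that allow for the imputation. Report how far apart the missing patients in the two arms would have to be for the conclusion to change, together with the share missing by arm, so that readers can judge whether such a gap is plausible.

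Do not make survival of both opposite-direction reruns a pass/fail rule: a true three-month effect with 20% random loss would fail it in about 70% of significant trials.

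The cost is a sentence or two of text and a little more analysis on the same data. The primary result may look less robust than the planned check would show.

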### Stopping rule

During the nine-month periapical radiographic assessment, if severe OIIRR (more than one third of the root Malmgren et al. [13]) is found in the majority of patients in one group, whilst the other group shows minor changes, then a trial monitoring committee will be convened to consider whether the study will be terminated.

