#### Secondary outcomes

The first secondary outcome will be the treatment outcome. This will be measured by evaluating the quality of treatment, the effectiveness of the appliance in delivering torque and the improvement in dental attractiveness. The quality of the treatment result will principally be measured by assessing the occlusal outcome using the Peer Assessment Rating Index (PAR Index) from study models recorded at the start and end of treatment. The torque of the maxillary incisors will be used to evaluate the effectiveness of appliance in delivering effective torque by measuring the angle between the long axis of the central incisors and the maxillary base from lateral cephalograms towards the end of treatment. The improvement in the dental attractiveness of the patient will be calculated using the aesthetic component of the IOTN. This will be evaluated by comparing the patient rating to the attractiveness of his or her teeth before and after treatment.

The second secondary outcome will be the biological side effects of the treatment, as measured by the amount of OIIRR. OIIRR will be established from periapical radiographs recorded at nine months into active treatment. Patients who show evidence of marked OIIRR will be treated in accordance with current recommendations.

The third secondary outcome will be the patient’s perception of wearing the fixed orthodontic appliance and of treatment outcome. This will be recorded using a questionnaire (Smiles Better) at six months after the start of treatment. Patient perception of the of fixed appliance treatment outcome will be measured by comparing patients’ pre-treatment and after-treatment questionnaires.

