### Trial Monitoring Committee

A Trial Monitoring Committee will be established, composed of three researchers (DB, GM and AE). This committee will meet every three months to monitor and discuss data for this trial. If it is found that one intervention particularly is causing significant harm to the dentition then the committee will have to decide to terminate the trial and shift all the study participants to the other intervention.

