## Trial status

The current trial is open for recruitment since January 2010 and is expected to reach the target enrolment of 216 participants in September 2014.

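### The root-resorption trigger misses a large one-arm excess below 50% and any severe harm common to both arms, and it does not match the monitoring committee's own criterion

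*Protocol article*

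**What the plan says.** The Stopping rule section of the protocol article ties the trigger to one time point, "During the nine-month periapical radiographic assessment", and to two conditions that must hold together. The first is "if severe OIIRR (more than one third of the root" on a cited grading), and it must be such that it "is found in the majority of patients in one group, whilst the other group shows minor changes". The consequence is a review: "then a trial monitoring committee will be convened to consider whether the study will be terminated". The section does not define minor changes.

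The Trial Monitoring Committee section describes a standing body of three researchers: "This committee will meet every three months to monitor and discuss data for this trial". Its criterion and consequence differ: "If it is found that one intervention particularly is causing significant harm to the dentition then the committee will have to decide to terminate the" (the quote is cut here). On termination, every participant would be moved to the other appliance. No threshold is given.

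For individuals, the Secondary outcomes section says: "Patients who show evidence of marked OIIRR will be treated in accordance with current recommendations". No section provides for a trial-level review when severe resorption is frequent in both groups.

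**The concern.** Root resorption is the harm that the trial sets out to compare. The Background names it as the most common adverse effect on the roots, and it is a secondary outcome. The Stopping rule is the only place where a numerical level of harm prompts a trial-level review.

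Both of its conditions limit what it can detect. Requiring a majority means that a difference between arms can be large and beyond doubt statistically without reaching the trigger. Requiring only minor changes in the other arm means that frequent severe loss in both arms switches the rule off. Two sections also give the committee different criteria and different consequences, so it would not know which to apply. At stake is a review that does not take place while patients, some as young as 12, are still being recruited and treated.

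**Working it through.** **Inputs.** Allocation is 108 per arm (Abstract). Evaluable number is 92 per arm (Target sample size). Meetings are every three months (Trial Monitoring Committee). Recruitment runs from January 2010 and "is expected to reach the target enrolment of 216 participants in September 2014" (Trial status), about 57 months. With even accrual assumed, that is 216 / 57 / 2 × 3 = 5.7, or about 6 patients per arm per quarter. The protocol states no expected rate of severe resorption, so every rate below is an assumption, with a range shown.

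**The plan's own figure.** The stopping rule states no error rate to reproduce. The 92 per arm does reproduce: 2 × (1.960 + 0.842)² × 7.2² / 3² = 90.4, so 91 by the normal approximation. The t-test solution is 91.4, rounded up to 92, with 80.3% power.

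**Step 1: one-arm excess, full data.** A majority is at least 47 of 92 or 55 of 108. The probability is the binomial upper tail P(X ≥ k | n, p).

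| True severe rate | P(≥ 47 of 92) | P(≥ 55 of 108) |
|---|---|---|
| 20% | 3e-11 | 8e-13 |
| 30% | 0.00002 | 0.000004 |
| 40% | 2.0% | 1.4% |
| 45% | 14% | 13% |
| 50% | 46% | 46% |

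Observed counts of 37/92 (40%) v 2/92 (2%) give Fisher p about 5e-11, and 28/92 (30%) v 2/92 gives p about 1e-7. Neither meets the rule.

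**Step 2: one-arm excess, repeated looks.** The rule can also be read as applying to the films available at each meeting. I simulated looks at 6, 12, ..., 90 films per arm. Minor changes was read either as no severe case in the other arm or as at most 10% severe. The chance of meeting the rule at some look is:

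- 40% v 2%: 26% to 33%
- 30% v 2%: 8% to 9%

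Most of this comes from the first small looks. If looks begin at 24 films per arm, the figures fall to 10% to 18% and about 1%.

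**Step 3: harm in both arms.** This follows from the wording alone: if severe loss is common in both arms, neither shows only minor changes. As an illustration, at 60% severe in each arm a given arm of 92 has a majority with probability 97%. The joint rule is met with probability about 0 on full data and about 0.5% over quarterly looks.

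**Step 4: firing by chance.** Let both arms have the same rate p, with m films per arm and minor changes read as no severe case. The chance that either arm triggers is 2 × P(majority of m | p) × (1 − p)^m.

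| Common rate | 1 film per arm | 3 films per arm | Quarterly looks, about 6 more per arm each |
|---|---|---|---|
| 5% | 9.5% | 1.2% | 0.01% |
| 10% | 18% | 4.1% | about 0.15% |
| 20% | 32% | 11% | about 1% |

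**Step 5: the two sections side by side.**

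| | Stopping rule | Trial Monitoring Committee |
|---|---|---|
| Criterion | Majority severe in one arm, minor changes in the other | Significant harm particular to one intervention, no threshold |
| Committee | Convened when the criterion is met | Standing, every three months |
| Consequence | Termination considered | Termination, and all participants moved to the other appliance |
| Harm in both arms | Excluded by wording | Not addressed |

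**The case against.** The strongest reply is that the Stopping rule does not stand alone. The standing committee sees data every three months and may act on significant harm from one intervention, without a majority and without a condition on the other arm. A 40% v 2% excess is the kind of harm that provision addresses. Patients with marked resorption are managed individually, and adverse events are recorded. This stands in part: a one-arm excess is partly covered, though by a criterion with no level. Harm in both arms is not covered, because that provision is also comparative.

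A reader might infer that the rule cannot fire for a real excess. The documents do not support this. No look schedule or minimum number of films is fixed, and on a running count a 40% v 2% difference triggers in roughly a quarter to a third of trials. A reader might also infer that the rule is prone to false alarms. That is confined to the first one to three films per arm, is about 1% or less at quarterly looks for equal rates up to 20%, and would lead only to a review.

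It is also fair that a journal article may leave the denominator and the minimum number of films to a fuller protocol, so their absence carries little weight here. The rates are assumed, and an unadjusted Fisher test is not a stopping standard. It serves here only to show how clear the ignored data would be. Lastly, a comparative rule suits a trial of two appliances in routine use. That explains the form of the rule, but does not provide a review when both arms do badly.

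**Conclusion.** The concern holds in a limited form. As stated, the joint condition ignores a large and highly significant excess that remains below half of one arm. With 92 per arm and a single look at full data, the rule is met 2.0% of the time at a true 40% and about 0.002% at 30%. Even with quarterly looks, a 40% v 2% difference goes untriggered in about two thirds to three quarters of trials. The exclusion of harm in both arms needs no assumed rate, because it follows from the wording. The two sections give different criteria and consequences and must be reconciled.

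The documents do not support saying that the trial has almost no protection: the standing committee has a broader one-arm criterion. The figures rest on assumed severe rates, even accrual and two readings of minor changes. The point is worth acting on because the remedy is cheap and concerns patient safety. It does not affect the primary analysis.

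**What to change.** At each three-monthly meeting already planned, give the committee a table of severe resorption on the nine-month films, by coded arm and pooled. Use the number of films read as the denominator, and give an exact confidence interval for the difference between arms. The by-arm rows bring a sub-majority excess to review, and the pooled row does the same for harm in both arms.

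Reconcile the Stopping rule and Trial Monitoring Committee sections into one criterion and one consequence. The trigger condition, the meaning of minor changes if that condition is kept, and the level that leads to termination are for the sponsor and its clinical advisers to set. The Outcome measures section places anonymization at the end of the trial, before any scoring, so it should also say that these films are read by coded arm during the trial.

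The cost is a protocol wording change and one small table per meeting. The downside is more frequent discussion of small counts and some false alarms.
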